## Abstract

**Background:**

Stereotactic body radiation therapy (SBRT) using intensity-modulated radiotherapy (IMRT) with dose escalation by simultaneous integrated boost (SIB) can be a safe modality for treating spinal bone metastases with enhanced targeting accuracy and improve local tumor control.

**Methods/Design:**

This is a single-center, prospective, randomized, controlled trial. One hundred and twenty patients with spinal bone metastases will receive palliative radiation therapy at the Heidelberg University Hospital. SBRT will be given in five or ten fractions with or without SIB. Four treatment arms are planned: IMRT with 30 Gy in ten fractions, IMRT with 30 Gy in ten fractions and SIB to 40 Gy, IMRT with 20 Gy in five fractions, and IMRT with 20 Gy in five fractions and SIB to 30Gy in five fractions will be compared. The target parameters will be measured at baseline level and at three and six months after radiation.

**Discussion:**

The primary endpoint of this study was to assess and compare the local tumor control (by means of different fractionation schedules and biological doses to the tumor area). Secondary endpoints are acute and chronic adverse events, pain relief, quality of life, and fatigue.

**Trial registration:**

ClinicalTrials.gov, NCT02832765. Registered on 27 July 2016.

**Electronic supplementary material:**

The online version of this article (10.1186/s13063-018-2452-7) contains supplementary material, which is available to authorized users.

## Background

Two-thirds of all cancer patients develop bone metastases during the course of their disease [1]. This form of distant relapse occurs from many types of solid cancers, especially from lung, breast, and prostate [2]. Bone involvement can also be extensive in certain hematologic malignancies [3, 4]. About 30% of all skeletal metastases and 10% of all primary bone tumors are located in the spinal column [5], mostly the lumbar (52%), thoracic (36%), and cervical (12%) spine [6]. The exact mechanism of bone metastasis is not fully understood. It is postulated that bone metastases arise as a detachment of tumor cells from the primary tumor and reach the bone by intravascular penetration, resulting in adhesion in distinct bone areas. The tumor cells cause local changes of the bone structure, caused by an imbalance of bone remodeling. Bone metastases present as osteoplastic, osteolytic, or mixed osteolytic/osteoplastic tumor masses. Many metastatic bone lesions cause few or no symptoms, but for skeletal-related events, pain is the most common symptom; many patients with bone metastasis experience significant pain at some point during their disease course [7]. Other skeletal-related events include reduce activity in daily life (ADL), decreased energy, hypercalcemia, and risk of pathological fractures and neurological deficits. Pathologic bone fractures occur in 5% and spinal cord compression in 10–15% [5]. Restrictions of movement of the spinal column may have a devastating long-term impact on function, mobility, independence, health, and quality of life (QoL). External beam radiotherapy has an established role in the management of patients with bone metastases of the spine. The fractionation schedule applying 30 Gray in ten fractions is a safe and effective treatment modality commonly used to achieve palliation of pain associated with spinal metastases [8]. In about 50–80% of the patients, a decrease of pain is reported and about 30% of the patients showed complete remission of pain [8]. Stereotactic body radiation therapy (SBRT) using intensity-modulated radiotherapy (IMRT) can be a safe treatment option for treating spinal metastasis with enhanced targeting accuracy [9, 10]. Published data report that IMRT to the spine was well tolerated, had no significant late toxicities, and spared other organs at risk [11]. Pre-treatment megavoltage computed tomography (CT) allows for the control of the patient position and improves treatment accuracy [12].

This study aims at evaluating therapeutic outcomes in terms of local control through a higher biological dose in the tumor area by using SIB-IMRT and to test shortened fractionation schedules in palliative patients. Toxicity, fatigue, and QoL improvements will be evaluated. To the best of our knowledge, no comparable randomized study has been described in the literature so far.

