## Methods/Design

This is a prospective, randomized, single-center, controlled, exploratory intervention study with four parallel treatment groups aimed at comparing local control rates after RT with and without SIB in patients with bone metastases of the spine. Four different schedules will be evaluated: IMRT with 30 Gy in ten fractions to the whole vertebral body, IMRT with 30 Gy in ten fractions to the whole vertebral body with the application of a SIB to 40 Gy, 20 Gy in five fractions to the whole vertebral body or IMRT with 20 Gy in five fractions to the whole vertebral body with the application of a SIB to 30 Gy. Before enrolment in the study, patients will receive CT and if necessary magnetic resonance imaging (MRI)-based staging examinations to measure the spinal cord dimension. If intraspinal metastases are suspected, an MRI examination is performed beforehand.

RT is performed in systemic/targeted therapy free interval. Radiation therapy will be applied in five fractions per week (Monday to Friday).

After recording the baseline measurements, patients will be randomly assigned to one of the four groups. Target parameters will be measured and recorded at baseline (t_1_), at week 12 (t_2_), and again at week 24 (t_3_) (Fig. 1). Follow-up measurements are scheduled to take place at 12, 18, and 24 months after the completion of RT (Fig. 2).

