### Recruitment and randomization

The patients will be given all the relevant information about the study by the radiation oncologist at their first presentation to our department (approximately 1–2 weeks before the start of RT). If patients are interested in participating in the study, they will receive a second appointment in order to further inform them and to obtain informed consent. A block randomization procedure will be used to ensure even distribution of patients into the four groups. The randomization procedure will be carried out by a central office. The study personnel responsible for the recruitment and patient care will have no access to the randomization information and the study director will have no influence on the recruitment of patients. The recruitment phase will be concluded with the attainment of the planned number of patients (120 patients in total, 30 patients in each group). Projected recruitment time will be 12 months, and recruitment is scheduled to start in February 2017. Regular study follow-up will end two years after enrolment or, where applicable, with the respective patient’s death.

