### Statistical analysis

Due to the explorative character of this study, it was not possible to estimate the total number of cases; with a scheduled number of 30 patients per group, it will, however, be possible to detect a standardized mean-value effect (Cohen’s d) of 0.74 with a power of 80% and a significance level of 5%, if a one-factorial variance analysis is calculated. All variables will be analyzed descriptively by tabulation of the measures of the empirical distributions. In case of continuous variables mean values, standard deviations, median, minimum, and maximum values will be documented. Categorical variables will be documented as occurrence and percentage. The primary endpoint will be measured by CT. Results will be presented at three months after completion of RT and differences between groups will be calculated using a one-factorial variance analysis. Differences of categorical variables will be calculated with the Chi-square test. The survival analysis will be performed using the Kaplan–Meier method and log-rank test.

All statistical analyses will be carried out descriptively using SAS software Version 9.4 or higher (SAS Institute, Cary, NC, USA).

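### Shortened fractionation is a stated aim, but the four-arm variance analysis neither isolates five versus ten fractions nor shows how large a loss remains possible

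*Protocol article*

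**What the plan says.** The last paragraph of the protocol article's Background gives two aims. The first is "evaluating therapeutic outcomes in terms of local control through a higher biological dose in the tumor area by using SIB-IMRT". The second is "to test shortened fractionation schedules in palliative patients". The first has a direction, improvement. The second has none.

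Methods/Design calls the study exploratory and describes four parallel arms: ten fractions without and with a simultaneous integrated boost (SIB), and five fractions without and with SIB. Its design sentence names only one comparison, "comparing local control rates after RT with and without SIB in patients with bone metastases of the spine". Recruitment and randomization fixes the size: "120 patients in total, 30 patients in each group".

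Under Statistical analysis, the primary endpoint is presented at three months and "differences between groups will be calculated using a one-factorial variance analysis". Categorical variables get a Chi-square test and survival a log-rank test. The output listed is means, standard deviations, medians, ranges, counts and percentages. The section describes all analyses as descriptive, but it also quotes a detectable Cohen's d "of 0.74 with a power of 80"% at a 5% significance level.

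**The concern.** The four arms form a two-by-two layout, fractionation by boost, and each aim corresponds to one of its two factors. The named analysis ignores that layout. A one-factorial analysis over four arms spreads its sensitivity over three degrees of freedom and answers only whether the arms are all alike. A significant result would not say whether fractionation was responsible. A non-significant one would not say how much worse five fractions might still be.

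The second case matters more. Each five-fraction arm has a lower total dose than its ten-fraction counterpart (20 v 30 Gy, and 30 v 40 Gy in the boost), and the first aim ties local control to biological dose. A reader will want to know how much control, if any, shortening costs. A bare test result leaves that open, and the less precise the data, the more easily a non-significant result passes for similarity.

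**Working it through.** **Inputs.** From the document: 30 patients per arm, four arms, significance level 5%, power 80%, d = 0.74. Assumed: two-sided testing (sidedness is not stated), SD = 1 (effects are in SD units because no SD is given), and all patients evaluable (no drop-out rate is given). The true losses below are also assumptions, shown as a range.

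**Step 1: the plan's own figure.** Two-sample t-test, 30 v 30, 58 degrees of freedom, noncentrality 0.74 × √(30/2) = 2.87. Power is 0.805, and 80% is reached at d = 0.736. The stated 0.74 therefore reproduces, as the figure for one pair of arms. In the four-arm variance analysis (3 and 116 degrees of freedom), a largest difference of 0.74 gives power between 0.65 and 0.93, depending on where the other arms lie. The 0.93 applies when two arms differ from the other two by 0.74.

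**Step 2: chance of a non-significant result if both five-fraction arms are worse by L.**

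- Four-arm analysis: noncentrality 30 × 4 × (L/2)² = 30L², on 3 and 116 degrees of freedom.
- Pooled 60 v 60: noncentrality L × √(60/2), whose square is also 30L², on 1 degree of freedom.
- One pair, 30 v 30: noncentrality L × √(30/2).

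At L = 0.4 the first two carry the same signal, 30 × 0.16 = 4.8. The four-arm test dilutes it over three degrees of freedom.

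| True loss (SD) | Four-arm analysis | Pooled 60 v 60 | One pair 30 v 30 |
|---|---|---|---|
| 0.3 | 76% | 63% | 79% |
| 0.4 | 59% | 42% | 67% |
| 0.5 | 39% | 22% | 52% |
| 0.6 | 22% | 10% | 37% |
| 0.74 | 7% | 2% | 20% |

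**Step 3: what an interval would show.** Half-width of the 95% interval = t × √(2/n).

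- 30 v 30: 2.002 × √(2/30) = 0.52 SD.
- 60 v 60: 1.980 × √(2/60) = 0.36 SD.

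An observed difference of exactly zero would thus still leave a loss of about 0.52 SD (one pair) or 0.36 SD (pooled) not excluded.

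**Step 4: pain response.** The Background reports a decrease of pain in 50–80% of patients. Taking the midpoint of 65% as an assumption, 1.96 × √(2 × 0.65 × 0.35/n) gives 24 percentage points at 30 v 30 and 17 at 60 v 60. At 50% the half-widths are 25 and 18 points; at 80% they are 20 and 14.

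**The case against.** The strongest reply is that the article claims nothing that this analysis fails to deliver. It calls the trial exploratory and the analyses descriptive. Its design sentence and its Discussion hypothesis concern the boost, so shortening is a subsidiary aim. A condensed article may leave contrasts and intervals to a fuller plan. Arm means and standard deviations will be reported, and a reader could build an interval from them.

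Much of this stands, and it rules out several stronger readings:

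- A reader might infer that the fractionation aim is a non-inferiority question with a missing margin. That is plausible for a shortened palliative schedule, but the document states no direction and never uses non-inferior or equivalent for this aim.
- A reader might infer that a null result will be taken as support for five fractions. No decision rule says so; the risk is one of misreading.
- A reader might infer that non-significance is the likeliest outcome even with a clear loss. At 0.4 SD that is true of the four-arm analysis (59%) but not of the pooled contrast (42%). At 0.5 SD it fails for the four-arm analysis too (39%).
- Extending the argument to the safety of the boost, as if non-significant neurological deficits would be taken as proof of safety, is a separate matter that the document does not raise.

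The reply does not remove the core. The article does not stay silent on method: it names a specific test and significance level for the primary endpoint, and that test does not address one of its two aims. An exploratory trial depends more, not less, on estimates with intervals.

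**Conclusion.** The point holds as a mismatch between a stated aim and the named analysis. The four-arm variance analysis does not isolate five versus ten fractions and puts no bound on the difference. With both five-fraction arms 0.4 SD worse it misses the loss in about 59% of trials, where a pooled contrast on the same patients would miss it in 42%. The uncertainty left is about 0.52 SD for one pair of arms and 0.36 SD pooled.

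These figures rest on two-sided 5% testing, unit SD, full evaluability and, for the pooled column, an equal loss in both boost strata. Missing three-month scans would widen the intervals. The 0.4 SD loss is illustrative; the document gives no loss that would matter clinically. The documents support neither a finding of a failed non-inferiority design nor one of an intended misuse of a null result.

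**What to change.** Add to the Statistical analysis section:

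1. The five-minus-ten-fraction difference with a 95% confidence interval for bone density, local control and pain response, pooled over boost and also within each boost stratum. For density this comes from a two-factor model of the arms already randomised. The within-stratum estimates show whether pooling is reasonable.
2. A sentence that a non-significant test is not evidence of similar efficacy.
3. The direction of the fractionation aim. Only if a not-worse conclusion is intended, fix the largest acceptable loss before outcome data are seen. For orientation, with a true difference of zero and one-sided 2.5%, the smallest margin testable at 80% power is (1.96 + 0.8416) × √(2/n): 0.72 SD at 30 v 30 and 0.51 SD at 60 v 60. Given the exploratory design, a formal non-inferiority test is not required.

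The cost is slightly more analysis and no extra patients; the Trial status section says recruitment was not complete. The drawback is that the fractionation result may have to be reported as inconclusive.

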## Methods/Design

This is a prospective, randomized, single-center, controlled, exploratory intervention study with four parallel treatment groups aimed at comparing local control rates after RT with and without SIB in patients with bone metastases of the spine. Four different schedules will be evaluated: IMRT with 30 Gy in ten fractions to the whole vertebral body, IMRT with 30 Gy in ten fractions to the whole vertebral body with the application of a SIB to 40 Gy, 20 Gy in five fractions to the whole vertebral body or IMRT with 20 Gy in five fractions to the whole vertebral body with the application of a SIB to 30 Gy. Before enrolment in the study, patients will receive CT and if necessary magnetic resonance imaging (MRI)-based staging examinations to measure the spinal cord dimension. If intraspinal metastases are suspected, an MRI examination is performed beforehand.

RT is performed in systemic/targeted therapy free interval. Radiation therapy will be applied in five fractions per week (Monday to Friday).

After recording the baseline measurements, patients will be randomly assigned to one of the four groups. Target parameters will be measured and recorded at baseline (t_1_), at week 12 (t_2_), and again at week 24 (t_3_) (Fig. 1). Follow-up measurements are scheduled to take place at 12, 18, and 24 months after the completion of RT (Fig. 2).

**Fig. 1 Fig1:**
[figure not shown]
*Flow chart* of IRON-2 trial; t0 = randomization, t1 = end of RT, t2 (3 months after RT) = restaging, t3 (6 months after RT) = restaging

**Fig. 2 Fig2:**
[figure not shown]
Timeline IRON-2: RT radiotherapy, IMRT intensity-modulated radiotherapy

### Recruitment and randomization

The patients will be given all the relevant information about the study by the radiation oncologist at their first presentation to our department (approximately 1–2 weeks before the start of RT). If patients are interested in participating in the study, they will receive a second appointment in order to further inform them and to obtain informed consent. A block randomization procedure will be used to ensure even distribution of patients into the four groups. The randomization procedure will be carried out by a central office. The study personnel responsible for the recruitment and patient care will have no access to the randomization information and the study director will have no influence on the recruitment of patients. The recruitment phase will be concluded with the attainment of the planned number of patients (120 patients in total, 30 patients in each group). Projected recruitment time will be 12 months, and recruitment is scheduled to start in February 2017. Regular study follow-up will end two years after enrolment or, where applicable, with the respective patient’s death.

### Inclusion criteria

Patients with histologic confirmation of a tumor disease, demonstrating metachronic solitary or multiple metastatic bone lesions of the thoracic or lumbar spine or the sacral boneIndication for RT of the bone metastasesMRI-based staging examinations (if necessary)Age 18–85 yearsKarnofsky Index ≥ 50% [13]Signed declaration of informed consent

### Exclusion criteria

Significant neurological or psychiatric disorders, including dementia and epileptic seizuresPatients with myeloma, lymphoma, or sarcomaPrevious RT to the treatment areaMSCCOther severe disorders that may prevent the patient’s participation in the studyDiminished legal capacityAny medical of psychological condition that the study director considers a preventive factor for the patient’s ability to complete the study or to adequately understand the scope of the study and to give his/her consent

### Assessment of the primary and secondary endpoints

The aim of the study is to evaluate local control rates in metastatic bone disease. The primary endpoint is defined by bone remodeling according to density in the metastasis. Bone density will be measured at the irradiated region at baseline and at the three-month time-point after the completion of RT (t_2_). Furthermore, the local control is assessed by CT imaging taken before and at three and six months after radiation treatment. Secondary endpoints are vertebral stability, QoL, fatigue, pain, overall survival, bone survival, pathological fracture, and neurological deficits. The baseline examination will be carried out immediately before the start of therapy and is scheduled to comprise the comprehensive recording of the socio-demographic data, the recording of the current pain situation (VAS score), the extent of fractures, the QoL, and the current degree of fatigue. The follow-up examinations will take place after the end of RT, as mentioned above (Fig. 1).

The secondary endpoints such as overall survival, fatigue, QoL, and anxiety will be recorded by using validated questionnaires (EORTC QLQ FA13 [14], EORTC QLQ BM22 [15], and the questionnaire to record stress in patients with cancer [FBK] according to Book et al. [16]). All patients will also be asked to record their pain history by using a pain diary (documentation of medication daily during treatment and once weekly after the completion of treatment, VAS pain scale). The pain response is documented on the VAS (range of 0–10). Complete response is defined as VAS score of 0/10 after three or six months and partial response is defined as a reduced value by at least 2 points after three or six months, according to the international consensus response categories by Chow et al. [17]. Overall survival is defined as time from initial diagnosis until death and bone survival is defined as time from initial diagnosis of irradiated spinal bone metastasis until death (Additional file 1).

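### Local tumour control is named as the primary endpoint and the aim, but the Methods define and analyse bone density as primary, and describe the region measured in two ways

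*Protocol article*

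**What the plan says.** All references are to the protocol article.

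**Local control as the question.** The Discussion paragraph of the Abstract states: "The primary endpoint of this study was to assess and compare the local tumor control". The Background closes with "This study aims at evaluating therapeutic outcomes in terms of local control through a higher biological dose in the tumor area by using SIB-IMRT". Methods/Design describes a trial "aimed at comparing local control rates after RT with and without SIB in patients with bone metastases of the spine". The section Assessment of the primary and secondary endpoints opens with "The aim of the study is to evaluate local control rates in metastatic bone disease".

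**Density as the endpoint.** The next sentence of that section reads: "The primary endpoint is defined by bone remodeling according to density in the metastasis". The one after it says "Bone density will be measured at the irradiated region at baseline" and again three months after radiotherapy. The text then continues: "Furthermore, the local control is assessed by CT imaging taken before and at three and six months after radiation treatment". The list of secondary endpoints that follows does not contain local control.

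**Analysis.** Statistical analysis says that the primary endpoint is measured by CT, that results are presented three months after radiotherapy, and that groups are compared by one-factorial analysis of variance. With 30 patients per group it gives a detectable Cohen's d of 0.74 at 80% power and a 5% level. Chi-square tests are planned for categorical variables, and Kaplan–Meier and log-rank methods for survival.

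**Volumes.** Radiotherapy identifies the gross tumour volume (GTV) with the metastasis and directs the boost at the macroscopic tumour. The target volume for the main prescription is the whole vertebral body with its posterior structures, plus 3 mm.

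**The concern.** A mean density and a proportion of patients with local control are different quantities. They need different summaries, tests and sensitivity statements. If the primary analysis is run as written, the trial reports whether mean CT density differs among four arms at three months. It does not report whether the boost raises the local control rate, which is the comparison announced in the Abstract and in Methods/Design. Because the Abstract gives local control the primary label, a difference in remineralisation could be presented as better control although control was not what the primary analysis measured.

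The region matters for the same reason. The boost acts on the metastasis. If density is read over the whole treated vertebra, boosted lesion and unboosted bone are averaged in the SIB arms, and non-tumour bone enters the measurement in every arm. The value obtained, and what it says about the boost, depends on which of the two descriptions the person measuring follows.

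**Working it through.** **1. Reproduce the plan's figure.** Inputs from Statistical analysis: n = 30 per group, d = 0.74, level 5% (two-sided assumed, since sidedness is not stated).

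- Noncentrality for two groups: d × √(n/2) = 0.74 × √15 = 2.866.
- Normal approximation: Φ(2.866 − 1.960) = Φ(0.906) = 81.8%.
- Exact two-sample t-test (noncentral t): power 80.5%; the d that gives exactly 80% is 0.736.

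So 0.74 reproduces as a comparison of two groups on a continuous outcome. For the four-group F test (3 and 116 df) the detectable largest difference depends on the pattern of means: 0.61 (two arms against two), 0.71 (one arm differs), 0.82 (equally spaced) or 0.87 (two extremes, the rest midway). Under any of these, the figure concerns a mean and not a rate.

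**2. Set the statements side by side.**

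| Place | Role | Quantity |
|---|---|---|
| Abstract, Discussion paragraph | primary endpoint | local tumour control |
| Background, last paragraph | aim | local control |
| Methods/Design | aim, SIB against no SIB | local control rates |
| Endpoint section, first sentence | aim | local control rates |
| Endpoint section, second sentence | primary endpoint | bone density |
| Endpoint section, later sentence | no stated rank | local control on CT at 3 and 6 months |
| Statistical analysis | primary analysis | CT measure at 3 months, ANOVA |

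The schedules differ as well: density at baseline and three months, local control before treatment and at three and six months. The text therefore treats them as two assessments.

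**3. Compare the two descriptions of the region.** One sentence places density in the metastasis (the GTV); the next places it in the treated region. Under Radiotherapy the second can mean the whole vertebra with posterior structures plus 3 mm. The GTV lies inside that volume but is not the same volume.

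**4. Does d = 0.74 say anything about control rates?** The article gives no planning rate. The only rate it cites is 93% at 24 months, from a series of 33 patients treated with SBRT and SIB (Discussion). Taking it for one group is an assumption, and so are all comparator rates. With p₁ = 0.93, p₂ = 0.83 and mean 0.88:

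power = Φ{ [ |p₁ − p₂|√n − 1.96√(2 × 0.88 × 0.12) ] / √(0.93 × 0.07 + 0.83 × 0.17) }

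- n = 30: (0.5477 − 0.9008)/0.4541 = −0.777, so power is 22%.
- n = 60 (two SIB arms against two arms without, 2 × 30): (0.7746 − 0.9008)/0.4541 = −0.278, so power is 39%.

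The same formula over a range of assumed comparators:

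| Assumed rate against 93% | 30 per arm | 60 per group |
|---|---|---|
| 70% | 64% | 91% |
| 80% | 31% | 55% |
| 83% | 22% | 39% |
| 85% | 16% | 29% |

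Power runs from 16% to 91% depending on inputs that the article does not supply. The table shows only that the published sensitivity statement does not transfer to a rate.

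**The case against.** The strongest reply is that the Methods are settled: the endpoint section defines density as primary, and Statistical analysis assigns CT at three months and ANOVA to the primary endpoint. Those two places agree, and only the Abstract attaches the primary label to local control; the other places state aims. This stands. A reader might infer that the plan leaves a free choice of primary result after the data are seen, but the operative text designates one primary analysis. The risk is mislabelling its result.

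A second reply is that density is meant as the working measure of local control. The wording allows the thought, but the article does not say it. It gives no threshold or direction of change and assesses local control separately. The Background notes that lesions may be osteolytic, osteoplastic or mixed, so a rise in density need not mean the same in each.

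Third, local control is not unanalysable, because chi-square and log-rank methods are in the plan, and the study is exploratory. Both are true. Exploratory status relaxes error control, but it does not reconcile two statements of what is primary.

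A reader might also infer that density is measured in two regions, or that the boost effect would be diluted by a known factor such as one half. Neither is supported. One measurement is planned, and the wider phrase may be only a loose locator. The article gives no lesion fraction and no standard deviation for either region, so no loss can be computed.

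**Conclusion.** The contradiction is in the current text and does not come from condensing a longer protocol: an analysis plan can add detail, but it cannot make the Abstract and the endpoint section agree. Followed as written, the plan yields a comparison of density that does not estimate the local control rate named as the aim. Local control itself has no event definition and no rank among the endpoints. The region of the density measurement needs one description.

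No numerical bias follows from the documents. A reader might conclude from the power table that the trial is too small for local control. That goes beyond the evidence, because the 93% is a 24-month rate from another series, this trial images local control at three and six months, and the comparator rates are assumed. The firm numerical result is that 0.74 is correct as a detectable difference in means between two groups and says nothing about a rate.

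**What to change.** Name one primary endpoint and use it in the Abstract, Background, Methods/Design, endpoint section and Statistical analysis. Two options are coherent.

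**Option A, which fits the existing ANOVA and sensitivity statement.** Make the primary endpoint CT density within the metastasis as contoured at baseline (GTV), from baseline to three months after radiotherapy. Take lesion type (osteolytic, osteoplastic, mixed) into account in the reporting, because the direction of change need not mean the same in each. Remove the reference to the wider treated region, or make whole-vertebra density a separate secondary measure. List local control as a named secondary endpoint with an event definition, analysed as categorical or time-to-event. Reword the Abstract and aims so that a density result supports a conclusion about remineralisation only.

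**Option B.** Make local control primary, with an event definition, a time point, a matching test and its own sensitivity statement, and make density secondary with its region fixed.

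Option A costs wording only, since the metastasis is already contoured and the CT scans are already planned; its downside is a narrower headline claim. Option B keeps the headline but requires a planning rate, which the article does not give, and a new sensitivity calculation.
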